## Abstract

**Background:**

Weaning is the process during which mechanical ventilation is withdrawn and the work of breathing is transferred from the ventilator back to the patient. Prolonged weaning is associated with development of ventilator-related complications and longer stays in the Intensive Care Unit (ICU). Computerized or Automated Weaning is a novel weaning strategy that continuously measures and adapts ventilator support (by frequently measuring and averaging three breathing parameters) and automatically conducts Spontaneous Breathing Trials to ascertain whether patients can resume autonomous breathing. Automated Weaning holds promise as a strategy to reduce the time spent on the ventilator, decrease ICU length of stay, and improve clinically important outcomes.

**Methods/Design:**

A pilot weaning randomized controlled trial (RCT) is underway in the ICUs of 8 Canadian hospitals. We will randomize 90 critically ill adults requiring invasive ventilation for at least 24 hours and identified at an early stage of the weaning process to either Automated Weaning (SmartCare™) or Protocolized Weaning. The results of a National Weaning Survey informed the design of the Protocolized Weaning arm. Both weaning protocols are operationalized in Pressure Support mode, include opportunities for Spontaneous Breathing Trials, and share a common sedation protocol, oxygen titration parameters, and extubation and reintubation criteria. The primary outcome of the WEAN study is to evaluate compliance with the proposed weaning and sedation protocols. A key secondary outcome of the pilot RCT is to evaluate clinician acceptance of the weaning and sedation protocols. Prior to initiating the WEAN Study, we conducted a run-in phase, involving two patients per centre (randomizing the first participant to either weaning strategy and assigning the second patient to the alternate strategy) to ensure that participating centres could implement the weaning and sedation protocols and complete the detailed case report forms.

**Discussion:**

Mechanical ventilation studies are difficult to implement; requiring protocols to be operationalized continuously and entailing detailed daily data collection. As the first multicentre weaning RCT in Canada, the WEAN Study seeks to determine the feasibility of conducting a large scale future weaning trial and to establish a collaborative network of ICU clinicians dedicated to advancing the science of weaning.

**Trial Registration Number:**

ISRCTN43760151

## Background

Weaning is the process during which mechanical ventilation is gradually or abruptly withdrawn. In addition, it is the time during which work of breathing is transferred from the ventilator back to the patient until fully autonomous breathing is resumed. Weaning accounts for approximately 40% of the total time spent on mechanical ventilation [1,2]. Invasive mechanical ventilation is associated with the development of important complications including ventilator associated pneumonia (VAP) [3], sinusitis [4], upper airway pathology [3] and respiratory muscle weakness [3]). VAP, in turn, is associated with increased morbidity and a trend toward increased mortality [5]. Mechanical ventilation has recently been identified as a key factor escalating intensive care unit (ICU) costs [6]. For these reasons, minimizing exposure to prolonged ventilation is an important goal of critical care medicine [7].

Over the past decade, research has focused on strategies to limit the duration of ventilation through early identification of weaning candidates [8,10], the conduct of tests of readiness to resume autonomous breathing [spontaneous breathing trials (SBTs)] [11,13] and strategies to reduce support in patients who fail a SBT [14,16]. Several modes and techniques are used to facilitate weaning. The optimal strategy to wean patients from invasive ventilation remains unclear. Compared to traditional care, protocols with their requirement for scheduled surveillance generally decrease the time to discontinuation and total duration of mechanical support [8-10]. Despite demonstration of large-scale implementation, many barriers exist to implementing weaning protocols in clinical practice including the requirement for broad, educational interventions and multidisciplinary compliance with them [17,18].

Automated weaning systems use closed-loop control to interpret clinical data in real time, perform basic and advanced ventilator functions and enable interaction between patients and the ventilator. Closed-loop systems adapt ventilator output by comparing measured values to targeted values of selected respiratory parameters and either minimizing or equilibrating (negative feedback) or amplifying (positive feedback) the differences between these values [19]. SmartCare™ is a unique automated system, specifically designed to guide weaning, that incorporates a closed-loop knowledge based system [20,21] into an automated protocol that adapts the level of pressure support provided to individual patient needs by operationalizing predetermined algorithms based upon respiratory rate (RR), tidal volume (V_T_) and end-tidal carbon dioxide (ETCO_2_).

To initiate SmartCare™ end-users enter the patient's weight, the presence or absence of chronic obstructive pulmonary disease (COPD) or a central neurologic disorder, type of airway prosthesis (tracheostomy or oro/nasal endotracheal tube) and the type of humidification (heated humidification or heat and moisture exchanger) in use. The first three parameters establish limits for RR, V_T _and P_ET_CO_2 _and the latter two items determine the threshold to cycle into a SBT (range: 5 to 12 cm H_2_O). SmartCare™ categorizes patients into one of 8 diagnostic categories based on average measurements of these parameters made every 2 to 5 minutes. With SmartCare™, patients may breathe with a RR ranging from 15 to 30 breaths/min (RR min) (alternatively, 34 breaths/min with neurologic disease) (RR max), a V_T _above a minimum threshold (V_T _Min = 250 ml if weight < 55 kg, or V_T _Min = 300 ml if weight ≥ 55 kg) and a P_ET_CO_2 _below a maximum threshold (max P_ET_CO_2 _= 55 mmHg or max P_ET_CO_2 _= 65 mmHg for COPD patients). SmartCare™ diagnosis a state of normal ventilation when a patient's ventilatory parameters fall within these ranges. If patient parameters fall outside of these ranges, an alternate diagnosis is made and the system adjusts the level of pressure support provided to attain these targets.

SmartCare™ automatically initiates a SBT when predetermined thresholds of pressure support are reached [22,23] in a state of normal ventilation with positive end-expiratory pressure (PEEP) is ≤ 5 cm H_2_O. This period is known as an 'observation period' and varies from 30 minutes to 2 hours in duration. Upon successful completion of a SBT, the ventilator issues a directive stating that the patient is "ready for separation from ventilator". Prior to extubation, physicians must ensure that patients meet readiness criteria to proceed with extubation. With SmartCare™, clinicians titrate the fractional concentration of inspired oxygen (FiO_2_) and PEEP. The automated algorithms may be applied during the day or during the day and at night.

SmartCare™ has been evaluated in physiologic studies and randomized controlled trials (RCTs). Similar to physician assessments using conventional pressure support, SmartCare™ was demonstrated in two physiologic studies to be capable of evaluating patient's ability to breathe spontaneously [22], decrease work of breathing, and reduce periods of respiratory distress during weaning [23]. A prospective cohort study of 42 intubated critically-ill patients, demonstrated that SmartCare™ could support ventilation over prolonged time periods (up to 12 days) [24]. Moreover, the system recognized patient's readiness to undergo a SBT earlier than intensive care physicians [24]. In a preliminary RCT involving 144 patients conducted in 5 European centres, Lellouche and colleagues showed that, compared to usual care directed by protocols in most centres, SmartCare™ decreased the median duration of ventilation from 4 to 2 days (p = 0.02), total duration of ventilation (9 to 6.5 days, p = 0.03), median ICU length of stay (15.5 to 12.0 days, p = 0.02) and nonsignificantly reduced the number of patients requiring prolonged ventilation (>21 days) (15.7 vs 6.7%, p = 0.11) [25]. Conversely, in a single centre RCT in Australia, comparing SmartCare™ to usual care in 102 patients, Rose and coworkers did not demonstrate reductions in weaning time or complication rates [26]. Moreover, the generalizability of results from these regions to Canada where weaning is a collaborative effort, involving registered respiratory therapists (RRTs) and intensivists, is unknown.

### Objectives

The primary objective of the multicentre pilot study comparing SmartCare™ [hereafter referred to as "Automated Weaning"] and "Protocolized Weaning" is to evaluate compliance with the weaning and sedation protocols among intubated patients requiring > 24 hrs of invasive ventilation.

The secondary objectives of the multicentre pilot RCT are to evaluate clinician acceptance of the alternative weaning and sedation protocols using a Visual Analogue Scale daily, and to demonstrate the ability to recruit the desired patient population. In this manner, we will assess the feasibility of conducting a future, definitive weaning RCT in Canada.

## Methods

### Study Design

A pilot RCT is currently underway at 8 adult ICUs across Canada in collaboration with the Canadian Critical Care Trials Group. Ethics approval for the study was obtained from the Research Ethics Board (REB) at St Michael's hospital and the REBs of participating centres. Figure 1 provides an overview of the study.

**Figure 1 F1:**
[figure not shown]
**Study Flow Diagram**.

### Run-in Phase

Prior to initiating the pilot RCT, we conducted a "run-in phase". The run-in phase included two patients at each centre. While, the first patient was randomized to either Automated Weaning or Protocolized Weaning, the second patient was assigned to the alternative weaning strategy in a non-random manner. Upon completion of the two patients, a clinical evaluation committee reviewed the completed case report forms to assess (i) the ability of participating centres to screen and enroll patients, (ii) compliance with study procedures, and (iii) timeliness of data collection and management. Approval from the clinical evaluation committee enabled sites to proceed to enrolling patients in the pilot RCT.

### Patient Screening

A dedicated research coordinator at each site screens patients for eligibility daily between 6:00 and 9:00 am at each site. We use a staged process to (i) identify potential study participants early in the weaning process and (ii) obtain consent for a Pressure Support Trials (PST). If patients fulfill the *Criteria for Consent *and have no exclusion criteria, a member of the investigative team approaches patients or their legal representatives for consent to (i) undergo a PST (once the *Criteria for a Pressure Support Trial *are attained) and a SBT (if criteria are met) and (ii) randomization depending on the outcome of the PST and SBT (see below).

### Criteria for Consent

We developed criteria to enable early identification of potential weaning candidates and to obtain consent early in the weaning process. These criteria include:

1) invasive ventilation for > 24 hours,

2) at least partial reversal of the condition precipitating invasive ventilation,

3) stabilization of "other" organ system failures (i.e. no worsening),

4) pulse oximetry oxygen saturation (SpO_2_) ≥ 90% with fractional concentration inspired oxygen (FiO_2_) ≤ 70%,

5) PEEP ≤ 12 cm H_2_O,

6) weight > 35 kg

7) the absence of exclusion criteria

We exclude patients (i) less than 16 years of age, (ii) with a do not reintubate order documented on chart or anticipated withdrawal of life support, (iii) prolonged cardiac arrest with poor neurological prognosis, (iv) a prior episode of invasive ventilation exceeding 24 hrs during the same hospital stay, (v) tracheostomy, (vi) pregnancy, (vii) known or suspected severe myopathy or neuropathy (i.e., Guillain-Barré syndrome) or quadriplegia, (viii) severe heart failure (grade 3 or 4 left ventricular function or New York Heart Association class 4 dyspnea).

### Criteria for Pressure Support Trial

We consider consented patients, who meet *the Criteria for Consent*, to undergo a PST at least once daily when they meet the following criteria:

1) intubated patient on mechanical ventilation,

2) SpO_2 _≥ 90% with FiO_2 _≤ 50% and PEEP ≤ 10 cm H_2_O,

3) no requirement for high dose vasopressors (i.e., no epinephrine or norepinephrine > 15 µg/min (or 0.2 µg/kg/min) or equivalent dose vasopressin or phenylephrine),

4) motor component of the Glasgow Coma Scale score ≥ 4 (withdraws to pain),

5) stable neurological status (no deterioration in the last 24 hrs, intact respiratory drive, and intracranial pressure < 20),

6) patient not expected to be extubated on the day of study randomization,

7) no surgery or procedure requiring sedation planned in the next 48 hrs.

We reassess criteria for a PST at least once daily after consent is obtained.

### Detailed Study Methods

#### Pressure Support Trials

PSTs are required to identify patients at the onset of the recovery phase when patients are first able to tolerate assisted ventilation. We adjust the level of pressure support provided to obtain a RR ≤ 35 breaths/min during PSTs. The initial level of pressure support is set at 15 cm H_2_O for patients not already on this mode and at the current level of pressure support in patients already on pressure support. PSTs are at least 60 consecutive minutes and not longer than 120 minutes in duration. The maximal pressure support (above PEEP) is 22 cm H_2_O and the minimum is 10 cm H_2_O. A PST can be stopped at any time for sustained hemodynamic or respiratory distress (heart rate ≤ 50 or ≥ 140 beats per minute or new significant dysrhythmias, systolic blood pressure ≤ 80 mm Hg or ≥ 180 mm Hg or RR > 40 breaths/min).

A PST is considered successful if after 60 consecutive minutes without a change in the level of pressure support, the patient remains clinically stable with a RR less than or equal to 35 and greater than 10 breaths/min with no decrease in pulse oximetry saturations (SpO_2 _remains ≥ 90% on an FiO_2 _≤ 50% with PEEP ≤ 8 cm H_2_O). Patients who fail a PST are returned to their previous ventilator settings or settings that restore respiratory comfort. We reassess these patients at least daily for criteria to undergo a PST. Patients who *successfully *complete a PST are assessed for a SBT. Patients who do not meet SBT criteria (i.e., are too early to undergo a SBT) are randomized upon successful completion of a PST.

#### Spontaneous Breathing Trials

Since patients who successfully complete a PST include those who *do *and *do not *require further weaning, we conduct an SBT with the goal of identifying patients who can tolerate pressure support but *fail *an SBT. These individuals are regarded as requiring further weaning. We consider patients with (i) partial or complete reversal of the cause of respiratory failure with SpO_2 _≥ 90% on an FiO_2 _≤ 0.4 (or at baseline level in chronically hypoxemic patients) and PEEP ≤ 5 cm H_2_O, (ii) hemodynamic stability [off vasopressors or on low levels of vasopressors (i.e., levophed ≤ 7 µg/min or ≤ 0.1 µg/kg/min) or equivalent], (iii) absence of uncontrolled sepsis, and (iv) stable haemoglobin > 70 g/L to undergo a SBT. We conduct SBTs of 30 to 120 minutes duration using either a T-piece with oxygen or continuous positive airway pressure (CPAP) ≤ 5 cm H_2_O or PSV of 5 - 7 cm H_2_O (using a heated humidifier or alternatively, 10-12 cm H_2_O with a heat and moisture exchanger) [27,30] with or without 5 cm H_2_O PEEP. Patients who successfully complete a SBT are considered for extubation (i.e., do not require further weaning). Conversely, patients who fail a SBT are randomized. We consider the presence of any one of the following: (i) RR > 35 breaths/min, (ii) clinical signs of respiratory distress (i.e., abdominal paradox), (iii) SpO_2 _< 90% (or below baseline in chronically hypoxemic patients) with FiO_2 _> 50%, (iv) systolic blood pressure ≤ 80 mmHg or ≥ 180 mmHg, (v) heart rate ≤ 50 or ≥ 140 beats/min or new significant dysrhythmias, (vi) severe agitation or diaphoresis, or (vii) Increased somnolence with elevated arterial pressure of carbon dioxide (PaCO_2_) and pH < 7.30 to signify SBT failure. In summary, we randomize consented patients requiring pressure support of at least 10 cm H_2_O who (i) successfully complete a PST, but DO NOT meet criteria to undergo a SBT (i.e., are too early to undergo a SBT) or (ii) who successfully complete a PST and fail a SBT.

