#### Study Randomization

Patients undergo stratified randomization within centres based on the presence (or absence) of (i) a diagnosis of known or suspected COPD [31,32] or (ii) a central neurologic disorder, provided that a study ventilator is available. In the event that both diagnoses are present, we prioritize central neurologic disorders during stratification.

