#### Statistical Analyses

Descriptive statistics including means, standard deviations, medians, interquartile ranges and frequency distributions will be used to summarize the data. For univariate analyses, we will use the Chi-square test (alternatively, Fisher's exact test when the expected value is ≤ 5) and Student's t-test (alternatively, the Mann-Whitney U-test, if normality assumptions are not satisfied) for binary and continuous outcomes, respectively. We will evaluate the percentage of (i) hours off-protocol and (ii) daily SAS scores < 2 or > 5 (or RASS equivalent) by treatment group. Compliance will be considered acceptable if ≥ 75% [that is; protocol violations (off protocol hours without meeting criteria to return to/remain on an alternate mode of mechanical ventilation) or SAS scores < 2 or > 5 (equivalent RASS -4 < or > +1) occur < 25% of the time]. SBT compliance will be considered acceptable if ≥ 75% of SBT opportunities are realized. We will compare average Likert scale scores based on clinician group and the weaning strategy utilized using Analysis of Variance (ANOVA). We will compare time to successful extubation and death between groups using time-to-event analysis with censoring of deaths and application of the log-rank test. We will consider p-values ≤ 0.05 to be statistically significant.

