## Conclusion

The WEAN pilot study was designed to evaluate clinician compliance with and acceptance of the proposed weaning and sedation protocols. In addition, we will ascertain whether centres can recruit the desired patient population. Strengths of the WEAN Study include the use of central randomization, allocation concealment, stratification (to ensure equal distribution of conditions that may prolong ventilation) and the use of protocols in both arms to limit treatment and performance bias. To this end, both treatment arms use pressure support and include opportunities to undergo SBTs. Moreover, they share a common PEEP/FiO_2 _chart, sedation protocol, extubation and reintubation criteria, and criteria for NIV use for post-extubation respiratory failure. The major threat to the validity of the pilot RCT is that it is, out of necessity, unblinded. To this end, we developed detailed weaning and sedation protocols to limit potential sources of bias and standardize weaning and sedation administration in both study arms and across participating centres. While we can not blind clinicians, patients and data collectors, we will blind the data analyst to treatment group assignment until the planned statistical analyses are completed. As the first multicentre weaning RCT in Canada, the WEAN Study seeks not only to determine the feasibility of conducting a large scale future weaning trial, but to establish a collaborative network of ICU clinicians dedicated to advancing the science of weaning.

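### Patients enter at two different points of weaning, and the log-rank comparison of time to successful extubation names no adjustment for entry route (minor)

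*Protocol article*

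**What the plan says.** The Spontaneous Breathing Trials section closes with two ways into the trial. Both need a passed pressure support trial (PST). One admits patients who "i) successfully complete a PST, but DO NOT meet criteria to undergo a SBT (i.e., are too early to undergo a SBT"; the other admits those "ii) who successfully complete a PST and fail a SBT".

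The Study Randomization section provides for "stratified randomization within centres based on the presence (or absence) of" COPD or a central neurologic disorder, the latter taking priority when both are present. The Conclusion gives the purpose as "stratification (to ensure equal distribution of conditions that may prolong ventilation". Entry route is not among the factors.

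The Study Outcomes section lists time to successful extubation, counted from randomization, as a secondary outcome; the primary outcome is compliance with the weaning and sedation protocols. The Statistical Analyses section compares extubation times by "time-to-event analysis with censoring of deaths and application of the log-rank test" and adds "We will consider p-values ≤ 0.05 to be statistically significant". It names no stratum or covariate. The Sample Size section sets 90 patients to assess compliance and states no power for extubation.

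**The concern.** Time zero is randomization, but it falls at two positions in weaning. A PST can be passed on FiO2 up to 50% and PEEP up to 8 cm H2O. The criteria for a spontaneous breathing trial (SBT) are tighter: FiO2 at most 0.4, PEEP at most 5 cm H2O, little or no vasopressor, no uncontrolled sepsis and stable haemoglobin. First-route patients miss at least one of these. Second-route patients met them all and then failed the trial.

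Route is known for every patient before allocation and could plausibly predict time to extubation. Yet nothing named in the article balances it or adjusts for it, and adjusting for COPD and neurologic disorder would not capture it. At stake are the precision of the extubation comparison and, if the arms happen to differ in route mix, the HR that readers would carry into a definitive trial.

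**Working it through.** **No planned figure to reproduce.** The article gives no effect size, event count or power for extubation, so what follows is illustrative.

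**Inputs from the article.** N = 90; 8 centres; three diagnosis levels (COPD, central neurologic disorder, neither); follow-up to 90 days; significance at 0.05.

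**Assumptions.** 45 patients per arm, two-sided test, exponential times, treatment HR 1.5 to 2, route HR 1 to 3, route share 30-70%, roughly 80 extubations or about 20% censoring.

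**1. Reference power with no route effect.** Power = Φ(|ln HR| × √(d/4) − 1.96). For HR 2 and d = 72 events: 0.693 × 4.243 − 1.96 = 0.98, so 84%. For HR 1.5 and d = 72: 0.405 × 4.243 − 1.96 = −0.24, so about 41%.

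**2. Simulated power, unstratified versus route-stratified log-rank, routes 50/50.**

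| Route HR | Treatment HR 1.5 | Treatment HR 1.8 | Treatment HR 2 |
|---|---|---|---|
| 1 | 40% v 39% | 71% v 68% | 84% v 81% |
| 1.5 | 39% v 39% | 71% v 71% | 83% v 83% |
| 2 | 37% v 41% | 67% v 71% | 80% v 83% |
| 3 | 33% v 41% | 57% v 71% | 73% v 85% |

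At treatment HR 1.8 the gain is 71 − 67 = 4 points at route HR 2 and 71 − 57 = 14 points at route HR 3. At treatment HR 1.5 or 2, with route shares of 30-70%, it is about 2-4 and 7-12 points. At route HR 1 stratifying costs about 2 points (83.7% − 81.4% = 2.3 at treatment HR 2). With no treatment effect, the unstratified test rejected in 4.8-5.6% of trials.

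**3. Chance imbalance.** With K first-route patients among 90, the number x falling in one arm of 45 is hypergeometric, and the difference in share is |2x − K|/45. For K = 45, a difference of at least 15 points means x ≤ 19 or x ≥ 26: probability 20.6%. For K = 27 or 63 it is 16.7%. A difference of at least 20 points has probability 6.5-9.1%.

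**4. Effect of an imbalance on the estimate.** With no treatment effect and an imbalance of about 15 points or more in one direction, the unstratified HR averages 1.04 at route HR 1.5, 1.12-1.14 at 2 and 1.20-1.22 at 3. The route-stratified HR stays at 0.96-1.03.

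**5. Route as a randomization stratum.** 8 × 3 = 24 cells, or 90/24 = 3.75 patients each. Adding route gives 48 cells, or 90/48 = 1.9 each.

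**6. Adding diagnosis to the analysis.** Crossing route with diagnosis gives 2 × 3 = 6 strata, on average 15 patients. I simulated this at treatment HR 1.8 (base rate 0.2/day, censoring 0.03/day, 90-day cap, diagnosis split 20/20/60, 8,000 trials per setting). If neither factor is prognostic, power is 74% unstratified, 72% stratified by route and 66% with six strata. A Cox model stratified by route with diagnosis as a covariate gave 70% (3,000 trials). If COPD or neurologic disorder halves the extubation rate and route HR is 2, the same four analyses give 59%, 64%, 65% and 70%.

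**The case against.** The article states nothing false here. It does not call the log-rank test unstratified; it merely names no strata, and an analysis plan not shown may supply them. Extubation is one of many secondary outcomes in a pilot sized for compliance, so there is no planned power to lose. The documents give no extubation times by route, and even the direction is open: a failed SBT shows difficulty, while a patient not yet eligible may recover quickly. Any baseline variable left out of the analysis could be criticised in the same way.

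Most of this stands, and it limits the point to a conditional and minor one. The last argument is weaker. Route is not just any covariate: the entry rule creates it, it is fixed before allocation, and it marks where in weaning the outcome clock starts. A stratified test needs no assumption about direction.

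A reader might infer more: that omitting route biases the treatment comparison, that power is certainly lost, or that the randomization should have been stratified by route. The documents support none of these. Randomization keeps the test valid, the loss depends on a route effect that nobody has quantified, and 48 cells for 90 patients would be too sparse to balance well.

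**Conclusion.** The point holds as a minor one about efficiency and about precision given the route mix that actually arises. The named comparison pools two starting points in weaning without adjustment. If route is strongly prognostic (HR about 2-3, an assumption), this costs about 4-14 points of power at a treatment HR of 1.8, and somewhat less at 1.5 or 2. An imbalance of 15 points or more, expected in about 17-21% of trials of this size, would then move a null HR to roughly 1.1-1.2 when the excess lies in one direction. At route HR 1.5 or less there is no power to gain. The sizes rest on 1:1 allocation, exponential times, the assumed censoring and the assumed HRs. The primary compliance outcome is not affected.

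**What to change.** In the Statistical Analyses section, state that the log-rank test and HR for time to successful extubation are stratified by entry route (not yet eligible for an SBT, or failed an SBT), together with the diagnosis factor used at randomization (COPD, central neurologic disorder, neither), and that the curves are shown by route. Do not add route to the randomization.

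The cost is wording and one binary baseline item that is already determined before allocation. Stratifying by route alone costs about 2 points of power if route is not prognostic. Crossing it with diagnosis into six strata costs more, about 8 points in step 6 (74% − 66%) if neither factor matters. Keeping route as the stratum and entering diagnosis as a covariate in the Cox model holds that to about 4 points (74% − 70%), so the wording should say which form is used.
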